### Data collection

Measures relating to both the overarching project aims and individual interventions will be collected pre- and post-intervention. Measures of service integration will be collected annually throughout the project for both control and intervention sites.

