Over the last three censuses (2012–2018), the Australian Capital Territory (ACT) has seen an increase in the proportion of children who are developmentally vulnerable on all but one of the AEDC domains and the two summary domains, vulnerable on one or more domains and vulnerable on two or more domains [10]. As a result, early childhood development has been a focus recently in the ACT. Early investigations have shown that services, organisations, and sectors continue to operate in isolation, and, as a result, it has been reported that families struggle to access cohesive and holistic pathways of care for their children. Examining the variation in early childhood vulnerability across suburbs making up the ACT’s nine districts reveals greater developmental vulnerability is experienced in clusters of suburbs. According to the 2018 AEDC, 26.4% of 5-year-old children in the Belconnen district were developmentally vulnerable in one or more domains [11].

An inventory of all early childhood services in the Belconnen district in 2019 revealed that there were multiple services across the education, health, and social services sectors in operation. These included but were not limited to Early Childhood Education and Care (ECEC) services, playgroups, preschools and parenting programs. However, evidence suggests that vulnerable families are unable to or choose not to access these services, or are not aware of them [12]. The fragmented nature of service delivery and accessibility, particularly across centres and services, hinders referrals and restricts pathways of care for children with developmental needs. Under these conditions developmental issues are not addressed, while the number of children entering school with significant social, communication, behaviour and health challenges continues to increase. Research confirmed that when such challenges are present on entering formal education, there are cascading effects throughout the school years and later in life [3, 4]. These children are more likely to experience poor academic achievement, early drop-out from school and unemployment [13].

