Literature on integration between early childhood centres reports that improving collaboration between services by creating more connected and productive early childhood programmes and networks provides better opportunities for positive outcomes for children and families [14]. Further studies have shown that the creation of a “virtual” network in which services do not need to relocate to a singular location produces the same benefits as co-located services [15].

As the nature of service integration prohibits a singular definition, a fit-for-purpose, context-and cultural- specific definition needs to be developed. In this project, the development of a definition will be considered as an outcome as this is an iterative process and will be refined throughout the project to represent the context, nature, and function of the integrated network most accurately. Broadly, this project views service integration as the creation of or strengthening of agency between early childhood services and programs across sectors within the local area. Such integration should provide a more comprehensive connection for families and greater numbers and quality of developmental opportunities for children, leading to better outcomes.

This project aims to evaluate an intervention designed to integrate child and family services within the district and embed allied health programs into early childhood education and care services and playgroups and to evaluate the outcomes and processes of the intervention. The Project Management Team (PMT) collaborate with local services to form a network of related services for children aged between birth and 5 years across the health, education, and social services sectors, allowing families to more easily access and navigate through different services.

The two main aims for this project are:

To create an integrated network of services for young children and families in target suburbs in the Belconnen district in the ACT.To reduce the proportion of developmentally vulnerable children in the target suburbs of the Belconnen district in the ACT.

The following questions will be addressed:

Does a multi-sector, multi-component approach reduce the proportion of children who are considered developmentally at risk in the intervention community compared to the control community?What is the reach, participation, intervention quality and dose of the interventions delivered and what were the barriers to, and facilitators of, implementation?

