## Methods and analysis

### Design and intervention

This study will use a quasi-experimental design to determine the effectiveness of creating an integrated service network on reducing developmental vulnerability in young children. The formative components of the project commenced in November 2020 and the project will conclude in March 2024. The intervention will take place in the Belconnen district, chiefly within services located in the nine identified target intervention suburbs, while the Tuggeranong district will serve as the ‘control’ site. These two districts are well-matched on socio-demographic characteristics and on early child development outcomes from the most recent three censuses. Data will be collected from the AEDC for comparison, but no intervention will occur within this district other than those that are to be expected in a large urban area. The intervention will be conducted using a ‘staggered’ approach, starting with four suburbs (in two clusters) in the first year and ending with all nine suburbs (four clusters) receiving the intervention by the fourth year. An integrated multi-sector programme will be delivered to children and families in multiple settings in the intervention suburbs through a wide range of programmes and services that focus on the 5 AEDC domains of childhood development: physical health and wellbeing, social competence, emotional maturity, language and cognitive skills, and communication and general knowledge. The list of programs to be implemented are presented in Appendix 1 in S1 File. To help achieve key aims of this project, a family liaison coordinator will be employed. The role of this coordinator will be to work within the community to connect families to services and to facilitate the creation of referrals for children with additional needs. In addition, the family liaison coordinator will work with services to better connect them to other related services and to the wider community.

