#### Service integration

Service integration will be measured mid-way through 2021 with respect to a 2019 baseline, and then annually for the duration of the project, using two validated tools. First, the Human Services Integration Measure (HSIM) by Browne et al. [18] will be given to all relevant organisations within the Belconnen district and all services and programs within the nine intervention suburbs. The tool (Appendix 3 in S1 File) is designed to gauge how each service perceives their current level of collaboration with other related services. To better reflect the context of the integration, the rating scale in the tool will be slightly adapted. Adaptations include a slight rewording of the rating explanations to better reflect the nature of service integration for early childhood centres and services and the addition of questions asking services to list the names of other services they have been involved with that did not appear on the survey. The tool will be distributed and completed using Qualtrics^XM^ (Qualtrics Australia, Sydney) online survey software. This will ensure the form is easy to complete and that all completed forms are returned and filed for data analysis.

The second tool, Successful Collaborations by Winkworth and White [19] will be administered to services that have indicated collaborations with other services on the HSIM tool. The Successful Collaborations tool (Appendix 4 in S1 File) aims to quantify the depth and scope of a collaboration between two services across three domains: capacity, authority, and shared value. The tool will be distributed, completed, and the data analysed online.

Representatives will also be invited to participate in a recorded interview. This interview will explore the collaboration in more depth and attempt to understand how service providers understand and use the term ‘integration’ and how they perceive the value and benefit of integrating services.

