This study has several limitations. The primary limitation arises from the use of the AEDC data. For confidentiality and privacy, the AEDC only releases suburb level data. However, it is widely understood that children do not always attend ECECs and services within the suburb in which they live. As a result, providing place-based interventions within intervention suburbs may not reach as many children from that suburb as intended. The study will collect data on which suburb each child attending a program or service lives in, but purposely excluding children from other suburbs is not possible as it is unethical and defies the universal nature of the programs and services provided.

It is known to the PMT that another similar project is operating in the Belconnen District at the same time as the Good Start in Life project. Whilst efforts have been made to regularly communicate and collaborate with the other project, there is the chance that their work may interfere with the two primary outcome measures of this project. Additionally, early childhood education centres, services and programs may elect not to engage with the study and to conduct their own professional development practices or engage with other services on their own. This may also influence the data this project is collecting on child development outcomes and service integration.

Finally, there is the chance that similar projects and interventions may operate within the control site, the Tuggeranong District. Once again, it is unethical and unfeasible to prevent other research teams or organisations from implementing similar programs in that area. However, throughout the study we will record any new programmes/services that are delivered in this control area.

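### Service integration is promised at both control and intervention sites, but the collection described names only Belconnen recipients, so the promised control data are not provided for

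*Protocol article*

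**What the plan says.** The first of the two main aims in the Introduction is "To create an integrated network of services for young children and families in target suburbs in the Belconnen district in the ACT". The limitations in the Discussion say of a similar project in the same district that "there is the chance that their work may interfere with the two primary outcome measures of this project". The text that follows names child development and service integration as the data that could be affected.

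On collection, the Data collection section states: "Measures of service integration will be collected annually throughout the project for both control and intervention sites". The Service integration section describes two tools. The HSIM "will be given to all relevant organisations within the Belconnen district and all services and programs within the nine intervention suburbs". The Successful Collaborations tool then goes to services whose HSIM answers show collaborations. On timing: "Service integration will be measured mid-way through 2021 with respect to a 2019 baseline", with annual rounds afterwards.

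On the control area, Design and intervention says that "the Tuggeranong district will serve as the" control site and continues: "Data will be collected from the AEDC for comparison, but no intervention will occur within this district". The only 2019 activity the article describes is "An inventory of all early childhood services in the Belconnen district in 2019", mentioned in the Introduction.

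**The concern.** Two sections give different instructions for the same outcome. A team working from Data collection would survey services in both districts each year. A team working from Service integration would survey Belconnen alone. The article does not say which governs.

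The choice decides what can be concluded about the first aim. With Belconnen data only, the result is a change over time in the area that received the programme. Services were disrupted in 2020, and the first described survey round is mid-2021, so some rise in reported collaboration could be recovery. Services asked every year to rate and name their partners may also report more simply because they are asked repeatedly. Neither can be told apart from a programme effect without a comparison area surveyed in the same way.

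The before-after comparison has a further weakness. Change is read against 2019, but the article does not say which instrument or which district(s) that baseline covers.

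**Working it through.** The article gives no sample size, power or significance level for service integration, so there is no figure to reproduce. The check sets the sections side by side.

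**1. Who receives each tool**

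| Source | Belconnen | Tuggeranong |
|---|---|---|
| Data collection (general promise) | yes, annually | yes, annually |
| Service integration, HSIM | 2 recipient groups (district organisations; services and programs in the nine suburbs) | 0 named |
| Service integration, Successful Collaborations | HSIM respondents reporting collaborations | 0, because it is nested in the HSIM |

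Quantitative analysis confirms that the intervention suburbs lie within Belconnen, so the second HSIM group adds no one outside that district.

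**2. Whether another section fills the gap**

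- Design and intervention mentions AEDC (Australian Early Development Census) data for Tuggeranong and no integration survey.
- Participants restricts invited services to the nine suburbs, or to partner organisations' services located in Belconnen.
- The Discussion adds a record of new programmes and services in Tuggeranong. That describes activity in the control area; it does not measure integration.

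None of the three provides control integration data.

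**3. How many rounds are affected**

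The first round is mid-2021 and the project ends in March 2024. Assuming the annual rounds stay at mid-year, they fall in 2021, 2022 and 2023. The control area therefore has three rounds under one section and none described under the other.

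**4. What a control would and would not remove**

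Write the change in Belconnen as programme effect + recovery common to both districts + repeat-survey effect + effect of the parallel Belconnen project. The change in Tuggeranong, surveyed on the same schedule, contains the common recovery and the repeat-survey effect. Subtracting leaves programme effect + parallel-project effect. This assumes that recovery and repeat-survey effects are similar in the two districts. The parallel project is specific to Belconnen and stays in the result.

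**5. The 2019 baseline**

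- Formative work began in November 2020. A 2019 baseline precedes it by 11 months (from December 2019) to 22 months (from January 2019), so its date is suitable for a pre-programme measure.
- The changes to the HSIM rating scale are written as still to come, and the form of any 2019 measurement is not stated. Equivalence with the later rounds is therefore not shown.
- No 2019 integration baseline for Tuggeranong is described.

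**The case against.** The strongest reply is that Data collection states the control measurement outright, and that neither Service integration nor Design and intervention says its list is exhaustive. In a condensed article, silence about Tuggeranong recipients need not mean exclusion. This stands in part: a reader might infer that the aim has no control at all, and the text does not support that. What it supports is that a promised control is not provided for where the collection is described, and that the two sections disagree.

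A second reply is that the first aim is worded for Belconnen, the between-community research question concerns child vulnerability, and the formal hypotheses cover only the six AEDC indices. This is also fair. No integration effect estimate is defined, so one cannot say that some share of it is uncontrolled. It does not remove the disagreement between sections, and integration scores are placed in the outcome evaluation.

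Three further inferences should be resisted:

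- A reader might take the 2019 baseline to be the service inventory or a recalled rating. The article says neither, and the sentence could mean that the two tools were applied to 2019 as well.
- A reader might take the 7 to 8 months from November 2020 to mid-2021 as programme exposure before the first survey. November 2020 is when formative components began; the date of first delivery is not given, and delivery is staggered.
- A reader might suppose that a control would deal with the parallel Belconnen project. It would not, and the Discussion already discloses that project as a limitation.

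**Conclusion.** The point holds as an internal contradiction affecting one of the two main aims: control data are promised annually, and the described collection names no control recipient for either tool. If the Service integration section is followed, the integration outcome is a Belconnen-only before-after change that cannot be separated from territory-wide recovery after 2020 or from repeat-survey effects. The size of any resulting bias cannot be calculated from the article.

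That recovery and repeat-survey effects would be shared by the two districts is an assumption, though a reasonable one for neighbouring services surveyed in the same way. On the baseline, the finding is only that comparability with the later rounds is not shown. The AEDC outcome is not touched by this point.

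**What to change.** **Preferred.** Amend Service integration so that both tools go to equivalent Tuggeranong services at every wave, using a Tuggeranong service list. Report the between-area difference in change from the first wave common to both districts:

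(Belconnen at wave *t* − Belconnen at first common wave) − (Tuggeranong at wave *t* − Tuggeranong at first common wave).

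Keep the parallel Belconnen project as a stated limitation.

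**If this is not done.** Remove the control site from the sentence in Data collection and describe the integration outcome as an uncontrolled before-after comparison.

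**In either case.** State which instrument and district(s) the 2019 baseline covers. Use it for change scores only if it came from the same adapted tools.

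**Cost.** The survey is already online and control collection is already promised, so the addition is modest. It is more than another mailing list, however: the HSIM form appears to list services, and the only inventory described is Belconnen's, so a Tuggeranong list would have to be compiled. Control services may respond less. If the first common wave is mid-2021, any integration gained in Belconnen before then will not show in the between-area estimate.

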#### Developmental vulnerability

The primary aim, to reduce the proportion of children who are developmentally vulnerable, will be measured by comparing results from the AEDC. A baseline measurement was recorded using the 2018 AEDC data for each intervention suburb. The comparative data will be taken from the 2024 AEDC results. The two timepoints will be analysed to see if there has been a significant decrease in the proportion of children in the ‘developmentally vulnerable in one or more domains’ category, as well as across all five EDI domains. The 2021 census data will not be used in this study due to disruptions to service delivery in 2020. Additionally, the interventions will have been running for less than a year at the time of the data collection, and therefore not enough dose will have been given to result in any significant impact on AEDC scores.

*Outcome measures*. Every three years the Early Development Instrument of the AEDC measures the five domains of early development described above in Australian children who are commencing their first year of full-time school. Under each of these domains, children are classified into one of three categories: developmentally on track, developmentally at risk and developmentally vulnerable. Summary indicators are then calculated for each community based on the proportions of children in each of these three categories. The primary focus for this study will be to reduce the proportion of children in the intervention community who are classified as developmentally vulnerable on one or more domains. We will also perform separate tests for significant change in the percentage of children at risk in each of the five individual EDIs.

*Sample size estimates*. Our sample size calculation is based on the AEDC ‘critical difference estimates for communities’ [17]. We will focus the intervention on those suburbs (SA2) in the two poorest performing districts with the highest proportions of children with at least one EDI domain in the developmentally vulnerable category at the most recent census. For example, based on 2018 census results, ~40% of this sample have been classified as developmentally ‘at risk’, i.e. falling significantly behind their peers, and could benefit from early intervention. We anticipate that approximately half of this number, ~250–300 children, will be required to show a statistically significant difference. Our primary focus will be on reducing the number of children who are developmentally vulnerable on at least one index (Table 1). We will also perform separate tests for change in the percentage of children at risk in each of the five EDIs.

**Table 1 pone.0267666.t001:** Critical differences (%) to establish significant change for each of the six early development indices.

Community size (# of children)	Developmentally vulnerable (1+) (%)	Physical Health & wellbeing (%)	Social competence (%)	Emotional maturity (%)	Language & cognitive skills (%)	Communication & general knowledge (%)
200–299	4.7	5	4.6	4.9	4.8	5.2

Time-point comparisons will be made between 2021 and 2024 AEDC indices for both intervention and comparator areas. Across-area comparisons will be made between intervention and comparator areas for the 2024 census indices.

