#### Quantitative analysis

Testing for statistically significant differences in children’s early development indices will be based on the critical difference approach developed for the AEDC by Gregory and Brinkman [17]. The Gregory and Brinkman report provides the technical details to determine “how big” a difference (%) needs to be in the EDI results between two different time points or two different areas to be considered statistically significant [11, Tables 14 –primary outcome and 13 –the five secondary outcomes, respectively]. The method allows for the expected sample to sample variation and typical measurement error associated with the sort of data collected in the AEDC. Current versions of the methodology allow us to compare two point-estimates, either across time or between neighbourhoods, of the selected index. Table 1 shows the critical differences that will be needed to establish a significant change for each of the six EDI indices,—the primary outcome and five secondary outcomes—to be considered in this study. The population of children in the intervention and control areas is expected to be in the range 200–299 at the 2024 census. Time-point comparisons will be made between 2021 and 2024 AEDC indices for both intervention and comparator areas. Across-area comparisons will be made between intervention and comparator areas for the 2024 census indices. The following hypotheses will be tested for each of the six indices to be used in this study:

Each EDI for the intervention suburbs (within the Belconnen district) for the 2024 census will be significantly lower, i.e. show a significant reduction in the proportion of children who are developmentally vulnerable or at risk, compared to that in the control suburbs (within the Tuggeranong district)Each EDI for the intervention suburbs (within the Belconnen district) for the 2024 census will be significantly lower, i.e. show a significant reduction in the proportion of children who are developmentally vulnerable or at risk, compared to the corresponding value in the 2021 census

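### The article rules out the 2021 census in one section but makes it the before-value of the time-point comparison and of hypothesis 2 in others

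*Protocol article*

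**What the plan says.** In the protocol article, the Developmental vulnerability section under Data collection names the two censuses for the before-after analysis. On the baseline: "A baseline measurement was recorded using the 2018 AEDC data for each intervention suburb". On the follow-up: "The comparative data will be taken from the 2024 AEDC results". It then excludes the census in between: "The 2021 census data will not be used in this study due to disruptions to service delivery in 2020". A second reason follows: "the interventions will have been running for less than a year at the time of the data collection", which the authors take to be too little exposure to move the scores.

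The sample size text, later in the same section, says: "Time-point comparisons will be made between 2021 and 2024 AEDC indices for both intervention and comparator areas". The Quantitative analysis section repeats that sentence. Its second hypothesis, stated for each of the six indices, requires the 2024 value in the intervention suburbs to be significantly lower "compared to the corresponding value in the 2021 census".

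The first hypothesis needs no earlier census: "Across-area comparisons will be made between intervention and comparator areas for the 2024 census indices".

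**The concern.** The article gives two different before-values for one comparison. Hypothesis 2 is the only stated hypothesis about change over time, and the Developmental vulnerability section ties the primary aim to such a change. An analyst who follows that section computes 2018 minus 2024. One who follows the Quantitative analysis section computes 2021 minus 2024, using data the article says it will not use.

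Two things are at stake. First, the 2021 version relies on a census that the authors rejected because services had been disrupted in 2020. Second, with both versions in print, either could be called pre-specified once the 2024 results are known.

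**Working it through.** **The statements side by side**

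| Place in the article | Before-value | After-value | Status of 2021 |
|---|---|---|---|
| Developmental vulnerability | 2018 | 2024 | not used |
| Sample size estimates | 2021 | 2024 | before-value |
| Quantitative analysis, time-point sentence | 2021 | 2024 | before-value |
| Quantitative analysis, hypothesis 2 | 2021 | 2024 | before-value |
| Quantitative analysis, hypothesis 1 | none | 2024, between areas | not needed |

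No sentence reconciles the first row with the next three. Neither the sample size text nor the Quantitative analysis section mentions a test of 2018 against 2024.

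**Number of tests affected.** There are 2 hypotheses and 6 indices, so 2 × 6 = 12 tests. Hypothesis 2 accounts for 1 × 6 = 6 of them.

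**Can the choice change the conclusion?** The contradiction needs no arithmetic, and there is no stated figure to reproduce. The following only illustrates what it could do.

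Inputs:
- Threshold for the primary index: 4.7 percentage points (Table 1, communities of 200–299 children). It comes from a cited report that is not at hand, so it is taken as printed and neither confirmed nor disputed.
- 2018 value: 26.4%, the Belconnen district figure in the Introduction, used as a placeholder for the target suburbs.
- 2024 value: 22.4%, assumed.
- s: the 2021 value minus the 2018 value, in points. The article gives none, so s runs from −3 to +3.

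Formulas:
- Fall from 2018: D18 = 26.4 − 22.4 = 4.0. This is below 4.7, so not significant.
- Fall from 2021: D21 = (26.4 + s) − 22.4 = 4.0 + s.

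| s | D21 | Reaches 4.7? |
|---|---|---|
| +3 | 7.0 | yes |
| +2 | 6.0 | yes |
| +1 | 5.0 | yes |
| 0 | 4.0 | no |
| −1 | 3.0 | no |
| −2 | 2.0 | no |
| −3 | 1.0 | no |

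Here the verdict flips once s reaches 4.7 − 4.0 = 0.7 points. In general D21 = D18 + s, so the 26.4% placeholder cancels. The two baselines disagree whenever D18 and D18 + s fall on opposite sides of 4.7. If D18 had passed the threshold, a 2021 value sufficiently below 2018 would remove the significance.

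**The case against.** Several points on the other side are fair.

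*The main between-area test is untouched.* Hypothesis 1 uses 2024 data only, the Abstract describes effectiveness as a comparison between areas in 2024, and the first research question is posed against the control community. This stands. It limits the reach to half of the hypothesis tests but does not settle which baseline hypothesis 2 uses.

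*The control area gives some protection.* Time-point comparisons are planned in both areas, so a recovery shared by both districts would show in the control district. This also stands, but only in part: hypothesis 2 concerns the intervention suburbs alone and does not net out the change in the control area.

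A reader might also infer more than the article supports:

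- *That 2021 is contaminated by the programme, so that early benefit would be subtracted.* The second reason for setting 2021 aside is the opposite premise: too little had been delivered by then to affect scores. Only the disruption argument speaks against 2021 as a before-value in the plan's own terms.
- *That a 2021 baseline would flatter the programme.* This needs a temporary rise in 2021. The article gives neither a 2021 value nor a direction for the effect of the disruption, and a lower 2021 value would make hypothesis 2 harder to meet.
- *That the baseline should be averaged over 2012, 2015 and 2018.* That belongs to a separate question about how suburbs were selected. It also does not fit the stated method, which compares two point estimates; nothing shown supports applying the 4.7-point threshold to a three-census average.

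**Conclusion.** The point holds as an explicit contradiction. The before-after test of the primary outcome and of the five domain outcomes cannot be run without breaking one of the article's own statements. It is not a detail left to a fuller document, because the article makes conflicting statements, one of them in a formal hypothesis. It should be corrected before analysis.

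Six of the 12 hypothesis tests are affected. The direction of any effect is unknown. The illustration shows that the choice of baseline alone can decide significance; it does not estimate what the 2021 data show. It rests on the assumed 2024 value, the assumed range for s and the printed 4.7-point threshold.

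**What to change.** Before the 2024 results are seen:

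1. Replace 2021 by 2018 in the time-point sentence of the sample size text and in the same sentence of the Quantitative analysis section, for both the intervention and the comparator area.
2. Reword hypothesis 2 so that the 2024 value is tested against 2018.
3. If 2021 is to appear at all, label it a descriptive or sensitivity point and correct the sentence in the Developmental vulnerability section that says it will not be used.

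The 2018 census is the natural choice because that section already records it as the baseline and explains why 2021 is set aside.

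The cost is a few sentences. No new data collection should be needed: 2018 results were already used to select the intervention suburbs, and the Design and intervention section says the two districts were matched on outcomes from the three most recent censuses.
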